## Discussion

Our study assesses a multi-faceted coordinated patient-centered strategy for treating LBP that incorporates the 4 main factors identified in the literature:

The management of psychosocial risk factors (10, 14).Active exercise reeducation program (40, 41).Tools for maintaining employment (12).Reinforced cooperation between primary healthcare professionals.

These factors are supposed to be clinically relevant for reducing the risk of persistent incapacity and extended sick leave and/or job loss in people presenting with LBP. At the chronic LBP stage, the benefits of strategies based on these factors remain modest and are often short-lived. The literature suggests that implementing these strategies at an earlier stage, when LBP is subacute or acute recurrent, may be more effective in reducing the risk of chronic incapacity. Thus, strategies need to be implemented in primary care (and not in the hospital setting) where early symptoms of LBP are managed. Furthermore, primary healthcare workers have the required competence to implement these strategies. Although, at present, there is not sufficient data to confirm this hypothesis. The French (13) and International recommendations (42–44) for treating patients with a risk of chronic LBP incorporate the 4 factors mentioned above. However, these recommendations are often based on expert consensus and not on evidence-based research. To date, the results of implementing strategies in primary care, only based on certain factors, have proved to be disappointing (45–48). We hypothesize that only the simultaneous implementation of strategies based on these 4 factors will significantly reduce the risk of chronic incapacity considered to be clinically relevant.

We decided to limit our study eligibility to adults younger than 60 years old. Indeed, the etiology of LBP varies with age. In adults younger than 60, the cause of LBP is mostly general and unspecific, becoming more specific with age. Beyond 70, the specific origin of LBP becomes clinically significant (33). Moreover, a critical portion of our study concerns the occupational impact of LBP. This impact becomes more difficult and/or less relevant to assess in patients older than 60 years because of the high probability of them being unemployed or retired.

GPs in the interventional group may preferentially include patients with severe LBP instead of enrolling all eligible patients if they consider the intervention to be better than usual care, and that this improved care may benefit patients with severe LBP more than patients with less severe LBP. This phenomenon may also occur in the control group, where GPs may be reluctant to suggest study participation because of the protocol’s constraints, to patients with non-severe LBP. We have examined this issue and will address this by providing continuous support for GPs during the study. Where a significant difference between groups in terms of patient’s LBP status at baseline is observed, we planned to adjust analyses to limit the impact of this bias on the results.

Most studies that have assessed the clinical evolution of LBP have used either pain, incapacity, and/or returning to work to measure the effectiveness of interventions (33, 49). However, from a patient’s perspective, reduced LBP is mainly comprised of three dimensions: attenuated pain, improved functional capacity, and combined with an acceptable quality of life, which includes the capacity to work (24). In our study, we chose perceived disability, considered by patients to be of utmost importance, as our primary outcome measure. However, we have included several secondary outcome measures, including measures to assess pain, quality of life, and the patients’ occupational status—other important facets of LBP.

Currently, in France, primary healthcare professionals, working in the same geographical region, are encouraged to group together in multidisciplinary practices. Our study is consistent with this evolution of primary healthcare, evaluating a coordinated strategy composed of a multidisciplinary team. Moreover, our study allows healthcare professionals in each region to form networks that hopefully will persist after the study has been completed. Consequently, we will cluster randomized GPs in the same region to promote local cooperation among professionals.

It has been reported that patient’s and healthcare provider’s expectations, based on previous experiences and representations, are associated with prognosis of patients with nonspecific LBP (50–52). Regarding patients, we believe that our randomized study design will limit the confusion bias from the heterogeneity in baseline patients’ expectations. Similarly, concerning healthcare providers, we expect that the randomized study design will equally distribute the healthcare providers’ expectations between the study groups at baseline. In addition, our study has been designed to evaluate whether the intervention will significantly change beliefs in healthcare provider’s, allocated to the Coordinated care group. This will be measured using the PABS (53). If required, an adjustment according to baseline levels has been planned.

In our study, the study intervention does not allow either the patients or providers to be completely blinded to the study group. Indeed, the study intervention involves not only specific actions from the GP but also informed patient participation, as an active partner in their care. We have done our best to limit information about the alternative group. For example, we created two different patients’ information and consent letters: one for each group. The information provided to patients has been adapted to the group allocated. In addition, the flow of information between groups are unlikely since GPs and their patients allocated the same cluster share the same geographical area, which differs to that of other clusters.

As in most clinical trials, our study may be affected by the “Hawthorne effect” or “trial effect” (54, 55). This effect concerns the changing of behavior due to study participation and the feeling of being observed. This may affect GPs in the control group, performing more careful treatment than usual, but may also occur in GPs allocated to the intervention group, with them having higher expectations and increased motivation. Therefore, it is difficult to estimate how, and to what extent, this effect could bias the study results.

This study will provide valuable data concerning the management of LBP in primary care in France. Overall, it will allow us to evaluate the benefit of a coordinated approach to LBP management, from the patients’ perspective, among other outcomes: to alleviate the associated disability, attenuate the pain, and to promote the return to work in patients suffering from subacute or recurrent acute LBP.

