### Primary objective and outcome

The primary objective is to assess the benefit of coordinated care for reducing disability, compared to usual care, in patients, aged between 18 and 60 years, consulting for subacute or recurrent acute LBP. The primary objective will be measured using the validated French version of the Roland Morris Disability Questionnaire (RMDQ) (20–22). The questionnaire comprises 24 questions and is scored from 0 (without disability) to 24 (with maximum disability). The primary outcome measure is the proportion of patients that has an improvement (lower score) of at least 4 points at 12 months after enrollment.

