### Secondary objectives and outcomes

The benefit of coordinated primary care, in terms of patients’ clinical improvement and employment status will also be assessed using the following secondary outcome measures:

The proportion of patients that have improved RMDQ scores by at least 4 points, relative to baseline, at 3 and 6 months after enrollment.The evolution of the RMDQ scores measured at baseline and then at 3, 6, and 12 months after enrollment.The proportion of patients that improved by at least 2 points on the numerical pain scale, relative to baseline, at 3, 6, and 12 months after enrollment. The numerical pain scale is widely used and validated by the French Health Authority (“Haute Autorité de Santé”) (23). The scale is assessed from 0 (no pain) to 10 (maximum pain). In the literature an improvement of 1.5 points is considered to the minimum improvement to be of clinical significance (24).The evolution of the numerical pain scale scores measured at baseline and then at 3, 6, and 12 months after enrollment.The proportion of patients that are “actively employed,” defined as being employed and being at work (not on sick leave), at 3, 6, and 12 months after enrollment. Patients on sick leave will not be considered as being actively employed.The number of days of sick leave during the 12 months after enrollment.The proportion of patients considered as having “improved overall.” Patients will be considered to have “improved overall” if they have improved their RMDQ scores by at least 4 points, improved their numerical pain scale by at least 2 points, and are actively employed. The outcome will be measured at 3, 6, and 12 months after enrollment.The change in the physical and mental quality of life of patients during the study measured using the Short-form 12 (SF-12). The SF-12 consists of physical and mental dimensions. Each dimension has 4 categories measure between 0 and a maximum value of 100. The higher the score the better the quality of life. The SF-12 is extensively used with a validated French version (25, 26). The SF-12 will be measured at baseline and at 3, 6, and 12 months after enrollment.The changes in the anxiety and depression scores of the Hospital Anxiety and Depression Scale (HAS). The HAS comprises 14 items: 7 for anxiety and 7 for depression (27). Each item is scored from 0 to 3. The HAS provides anxiety and depression scores ranging from 0 to 21. The study will use the validated French version and will be completed by patients at baseline and at 3 and 12 months (28).

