### Statistics

Quantitative data will be presented as means with standard deviations and will be compared using Mann–Whitney tests. Qualitative data will be presented as numbers with percentages and compared using Fisher’s exact tests.

For the primary objective, the proportion of patients that have an improved (lower score) of at least 4 points, in the RMDQ, at 12 months after enrollment will be compared in the study groups. The analysis will be performed using a multilevel logistic mixed model that will allow the clustering effect to be considered as random.

Similarly, the secondary outcome measures with binary outcomes compared between the study groups (e.g., the proportion of patients that improved by at least 2 points on the numerical pain scale at 12 months) will be analyzed by multilevel logistic mixed regression models.

Secondary outcome measures assessing changes in a quantitative parameter over time (e.g., the evolution of the RMDQ scores measured at baseline and then at 3, 6, and 12 months after enrollment) will be analyzed using linear multilevel mixed regression models. The individual effect will be included in the cluster effect. Time will be considered as qualitative variables with a varying number of modalities, e.g., 4 modalities for outcomes assessed at baseline, and then at 3, 6, and 12 months, and 3 modalities for outcomes assessed at baseline, and then at 3 and 6 months. The effect of the intervention will be evaluated by including an interaction between the variables for time and for the study group. The effect of the intervention will be assessed at each time point. The increased alpha-risk, due to multiple analyses, will be accounted for using the Bonferroni correction.

For these various multilevel models, the variance–covariance matrices will be considered as unstructured. Missing data will be treated using a set of 10 multiple imputations based on chained equations (38, 39). The analyses will be performed bilaterally with the alpha-risk set at 5%, except in cases where the Bonferroni correction was used. The data will be analyzed on an intent-to-treat basis. Thus, all patients with data will be included in the analysis unless they specifically indicate that they do not want their data analyzed.

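### Adjustment for baseline severity depends on a significant baseline difference; baseline RMDQ should be a fixed covariate in the primary model

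*Protocol article*

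**What the plan says.** In the Discussion the authors raise selective recruitment themselves. For the intervention arm: "GPs in the interventional group may preferentially include patients with severe LBP instead of enrolling all eligible patients". For the other arm: "This phenomenon may also occur in the control group, where GPs may be reluctant to suggest study participation", here for patients whose pain is not severe. Two remedies follow: continuous support for GPs, and a conditional analysis rule, "Where a significant difference between groups in terms of patient’s LBP status at baseline is observed, we planned to adjust analyses". The rule does not say which measure of LBP status is tested, which test is used, or which covariates would then enter.

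The Statistics section describes the primary analysis in one sentence: "The analysis will be performed using a multilevel logistic mixed model that will allow the clustering effect to be considered as random". No baseline covariate is named. For quantitative data in general, the section names the Mann–Whitney test.

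The endpoint is defined under Primary objective and outcome: "The primary outcome measure is the proportion of patients that has an improvement (lower score) of at least 4 points at 12 months after enrollment". The RMDQ runs from 0 to 24, and the eligibility criteria set no minimum score. Baseline RMDQ is collected from every patient (Table 1) and is used in a secondary outcome: "The evolution of the RMDQ scores measured at baseline and then at 3, 6, and 12 months after enrollment".

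**The concern.** Clusters are randomized first. Intervention GPs are trained before the study starts, and the Discussion concedes that neither patients nor providers can be fully blinded. Randomizing clusters therefore does not by itself protect balance between the patients enrolled. A baseline difference can be a real product of recruitment and not only chance.

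Baseline RMDQ is also part of the endpoint's arithmetic. A patient who starts at 0 to 3 cannot improve by 4 points, and a patient who starts higher has more room to do so. A severity imbalance thus moves the responder proportion even if the intervention does nothing.

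A significance test is a poor switch for adjustment here. It responds to sample size, whereas the bias depends on the size of the imbalance and on how strongly baseline predicts response. The test can miss an imbalance that matters and can fire on one that does not. Either way, the form of the confirmatory model is settled only after the baseline data have been compared by arm.

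**Working it through.** **The plan's own figure.** For 50% vs 70%, 80% power and two-sided 5%, the sample size is 93 per arm. The design effect is 1 + ((1 + 0.2²) × 25 − 1) × 0.03 = 1.75. Clusters per arm are 93 × 1.75 / 25 = 6.51, rounded up to 7, plus one small-sample cluster = 8. Allowing for attrition, 8 / 0.80 = 10 clusters of 25 per arm, or 500 in total. The stated 500 reproduces, and 250 enrolled per arm is used below.

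**Assumptions not in the documents.** Baseline RMDQ mean 11, SD 5; 12-month score regressed on baseline with slope s = 0.3 to 0.5; residual SD 5; about half of patients responding; baseline ICC equal to the outcome ICC of 0.03; Mann–Whitney at 5% as the trigger.

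**1. Effect of an imbalance if nothing is adjusted.** One extra baseline point raises the mean improvement by (1 − s). The SD of improvement is √((1 − s)² × 25 + 25). Near 50% response, the change in the proportion is about 0.399 × (1 − s) / SD.
- s = 0.3: 0.399 × 0.7 / 6.10 = 4.6 percentage points.
- s = 0.5: 0.399 × 0.5 / 5.59 = 3.6 percentage points.

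Simulation with no treatment effect gives 49.9% to 54.7% (s = 0.3) and 50.1% to 54.0% (s = 0.5) for a 1-point shift, that is 4.8 and 3.9 points. Baseline RMDQ explains about 16 to 23% of the variance in responder status.

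**2. How often the trigger fires.** An unclustered test works with SE = 5 × √(2/250) = 0.447. The true SE is larger by √(1 + 24 × 0.03) = √1.72 = 1.31.
- 1-point shift: 1/0.447 = 2.24, and Φ((2.24 − 1.96)/1.31) = 58%, so about 42% missed. Simulation: 57% fired, 43% missed.
- No shift: 2 × (1 − Φ(1.96/1.31)) = 13%. Simulation: 12%, against a nominal 5%.
- Range for a 1-point shift by baseline SD, same formula: SD 4, 26% missed; SD 6, 53% missed.

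**3. The rule as written, simulated.** No true effect, 20 clusters, 25 enrolled and 20 analysed per cluster, s = 0.35, 1,500 runs. Logistic models with cluster-robust SE and t(18) stand in for the mixed model.

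| True baseline shift | Trigger fires | OR, never adjust | OR when trigger does not fire | Average OR, planned rule | OR, always adjust |
|---|---|---|---|---|---|
| 0.5 | 25% | 1.11 | 1.06 | 1.05 | 1.00 |
| 1 | 57% | 1.22 | 1.10 | 1.05 | 1.01 |
| 1.5 | 83% | 1.31 | 1.13 | 1.01 | 0.99 |
| 2 | 97% | 1.46 | 1.10 | 1.00 | 0.99 |

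False-positive rates across these four rows are 7.5% to 32% if never adjusted, about 5 to 6% under the planned rule, and about 5 to 6% if always adjusted. At about half the planned enrolment, the trigger misses a 1-point shift in 65% of trials. The average OR under the rule is then still about 1.05; in trials where the trigger does not fire it is 1.10 (1-point shift) or 1.20 (2-point shift).

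**4. Scale.** From 50% response, OR 1.05 gives 1.05/2.05 = 51.2% and OR 1.10 gives 1.10/2.10 = 52.4%. These are shifts of 1.2 and 2.4 percentage points, against a design difference of 20.

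**The case against.** The strongest reply is that the planned rule works tolerably well. It catches the imbalances that would do most damage and keeps the false-positive rate near 5 to 6%, no worse than always adjusting. This stands, and it limits the size of the point.

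Three stronger readings are tempting and should not be drawn.

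- A reader might infer that the protocol expects sicker patients in the intervention arm, and so an inflated effect. It says only that selection may occur, and it describes a mechanism favouring severe patients in both arms. The net difference could be small and could go either way.
- A reader might take the unadjusted effect of a 2-point imbalance, about 8 to 9 percentage points, as the bias at stake. That describes an analysis that is not planned. With SE 0.447 (unclustered) or 5 × √(2 × 1.75/250) = 0.59 (clustered), a 2-point difference is significant in about 99% or 92% of trials, and adjustment would follow.
- A reader might cite the other conditional sentence in the Discussion, "If required, an adjustment according to baseline levels has been planned", as a second instance for patient severity. It follows the text on providers' beliefs and the PABS, so it does not bear on the RMDQ model.

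It can also be said that covariate lists usually belong in the analysis plan, and that a condensed article need not give one. That is right for silence alone. Here the article states a rule, and the rule is data-dependent.

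**Conclusion.** The point holds at modest size. The article fixes a rule under which baseline severity enters the primary model only after a significant baseline difference, for an endpoint built from baseline RMDQ, in a design where the authors themselves foresee selection by severity.

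The residual bias under that rule averages an odds ratio of at most about 1.05, and about 1.06 to 1.13 at planned enrolment in trials where the trigger does not fire. The false-positive rate shows little or no inflation. Direction is unknown. These figures rest on the assumed RMDQ distribution, slope and baseline ICC, and on Mann–Whitney being the trigger.

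Two costs do not depend on the exact figures. The primary model is chosen after seeing the data. Whenever the trigger does not fire, a strong predictor already in hand goes unused and precision is lost (in a logistic model this shows mainly as power). It would be wrong to say that precision is lost in every case: once adjustment is triggered, baseline status is in the model.

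**What to change.** Delete the significance trigger. State that the primary multilevel logistic model includes baseline RMDQ as a continuous fixed covariate whatever balance is observed, and report the model without it as a sensitivity analysis.

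Apply the same to the binary RMDQ and pain responder outcomes, each with its own baseline score. Do not extend it to the longitudinal linear models, which already carry baseline as a level of time, or to sick-leave days over the 12 months, which have no matching baseline value.

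State the limit as well: this corrects for measured severity only. Selection on unmeasured factors remains, and the planned support to GPs is still needed.

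The cost is wording. The scores are already collected at baseline and the sample size stays at 500. The change should be made and dated before anyone compares baseline data by arm; if that has already happened, the amendment should say so.

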## Future directions and clinical implications

Our study design is pragmatic and based on current healthcare practices in French primary care. Consequently, our results will have a high potential for transferability. They may support early collaboration between GPs, physiotherapists, and OPs for treating patients with subacute or recurrent acute LBP in primary care. More largely, they may also advocate for reinforcing interdisciplinary collaborative practices around patients having musculoskeletal disorders, pain syndromes, or other types of chronic conditions.

## Trial status

On the 5th of May 2023, 19 clusters have been initiated with the approval to include patients: 41 patients have been enrolled.

## Ethics statement

The CO.LOMB study was conducted in accordance with the guidelines of the Declaration of Helsinki, and respecting French and European regulations, including the European General Data Protection Regulation and the requirements of the French “Commission Nationale de l’Informatique et des Libertés”. The study has been approved by an independent French ethics committee, the “CPP Ile de France XI” (Study number 20.01298.067400-MS02). All participants provided written informed consent before participating in the study.

